### **1.5.2. Capsaicin**

When the TRPV1 receptor is activated by capsaicin, it may open transiently and initiate depolarization mediated by the influx of sodium and calcium ions. In the nociceptive sensory nerves which selectively express TRPV1 (mostly C- and some A $\delta$ -fibres), depolarization results in action potentials, which propagate into the spinal cord and brain, and may be experienced as warming, burning, stinging, or itching sensations.

### **1.5.3. Cowhage**

The cowhage spicule delivers to the skin a cysteine protein called mucunain that has been shown to be capable of activating the protease-activating receptors PAR2 and PAR4 [Reddy, 2008b]. PAR2 receptors have been implicated in the pathophysiology of itch and of AD. Cowhage stimulates nerve fibres distinct from those activated by histamine - C polymodal nociceptors which can transmit itch as well as other mechanical and noxious stimuli. [Namer, 2008; Schmelz, 2010].

#### **1.5.4. Histamine**

Histamine has been used for many decades as the experimental pruritogen of choice in numerous studies. [Melton, 1950; Ishiuj, 2009] In chronic pruritic disease the histaminergic pathway does not appear to be the most relevant pathway. However potent histamine H1 and H2 antagonists such as Doxepin have been shown to reduce pruritus significantly in a number of pruritic diseases such as AD, lichen simplex chronicus, contact dermatitis and nummular dermatitis, so histamine does play a role [Drake, 1994, Drake, 1995].

An understanding of the impact of SB705498 on pruritus initiated by cowhage or histamine may support the exploration at later stages of pruritic indications.

##### **1.6.2. Capsaicin**

Previous studies using 0.5ml of a 0.075% capsaicin cream (which equates to around 37.5µg), showed a reproducible response of flare to capsaicin at doses of around 30µg on the forearm when an oral dose of the TRPV1 antagonist SB705498 was administered [Chizh, 2007];and [Wang, 2010]

In a previous GSK study, a unilateral, intranasal challenge model using incremental doses (0.25 - 50 µg) of capsaicin in healthy subjects was evaluated [GlaxoSmithKline Document Number [GH2007/00009/00](#). Study ID VR1111611]. There was a dose-dependent increase in the weight of nasal secretions with increase in capsaicin dose. The maximum induction of nasal secretions was achieved in response to challenge with 50µg of capsaicin (Emax), whilst the dose of capsaicin that led to half maximal response (ED50) was 9.43 µg (CV: 26%). We therefore believe that an appropriate dose for this study will be 0.5mL of a 0.075% capsaicin cream (37.5µg).

### **1.6.3. Cowhage**

The number of spicules and method of application of the cowhage spicules is based on methodology used in similar studies of itch [[Papoiu](#), 2011]. Around 30-35 cowhage spicules will be applied to a 3x3cm square area on the skin of the forearm and gently rubbed in to facilitate contact. Personal communication from [name], based on his previous research, indicates that this number of spicules produce a reproducible sensation of itch.

### **1.6.4. Histamine**

Delivery of histamine will be done according to the skin prick method using 1% histamine solution [[Kofler](#), 2011]. This is a widely accepted method used in allergy clinics to test for histamine sensitivity; causing pruritus, skin flare and a skin wheal.

The formulation and dose of histamine is based on methodology used in similar studies of itch [[Papoiu](#), 2011].

## **1.7. Summary of Risk Management**

### **1.7.1. SB705498**

SB705498 (drug substance alone) and SB705498 formulated in cream shows some absorbance of light in the 290 to 700 nm wavelength range (minor peaks at 311 and 309 nm, respectively). which may indicate some potential risk associated with exposure to UV rays. There are several approved topical drugs that absorb within the visible light range. This includes topical calcipotriene/calcipotriol, used to treat psoriasis and topical retinoids approved to treat acne, psoriasis, and wrinkles. In order to minimize any potential photosensitivity risk it is advised that subjects should avoid excessive exposure to either natural or artificial sunlight (including tanning booths, sun lamps, etc.). Subjects should use sunscreen of at least SPF30 and wear protective clothing when outdoors for a week after the last dose of SB705498. Subjects should also avoid photosensitizing drugs (e.g, tetracycline, thiazides, fluoroquinolones, phenothiazines, or sulfaonamides). Subjects unwilling to adhere to this will not be included in the study according to the inclusion/exclusion criteria.

The anticipated systemic exposures associated with the proposed topical doses have been well tolerated in previous studies and are not expected to result in systemic adverse effects.

**Table 2** shows the potential systemic exposure and the corresponding safety margins following dermal administration calculated assuming 10, 20, 60 and 100% bioavailability at maximum daily doses of 10, 30 and 50mg, respectively. The highest observed systemic exposure (AUC) seen following BID administration of SB705498 at 12 mg (i.e. total daily dose of 24mg for 14d) for 14 days in the intranasal clinical study has been used to calculate dermal systemic exposures, assuming that the systemic exposure (AUC) scaling is linear. Safety margins have been calculated for the estimated AUCs relative to the previously defined GSK Global Safety Board (GSB) safety limit of 26 µg.h/mL in a 24 h period, and therefore represent worst case scenario. In the clinical protocol we have calculated, as a worst case scenario, the maximum dose likely to be administered as 45 mg over 2 days (Part A), and the maximum daily dose will be 50 mg (Part B). It is anticipated that the maximum systemic exposure following dermal administration of the maximum daily dose (50 mg) will be substantially lower than those achieved in the intranasal 14 day clinical study.

Based on previous experience with topical application of drugs and the amount of body surface area to be treated, it would be expected that <10% of the drug applied would be measured in the plasma.

**Table 2 Potential systemic exposures to SB705498**

| Cream strength (% w/w) | Max. Daily dose (mg) | % F | AUC (µg.h/mL) | fold safety cover |
|------------------------|----------------------|-----|---------------|-------------------|
| 5                      | 50 (2x 25mg)         | 100 | 15.8          | 1.52              |
|                        |                      | 60  | 9.50          | 2.53              |
|                        |                      | 20  | 1.90          | 12.6              |
|                        |                      | 10  | 0.190         | 126               |
| 3                      | 30 (2x15mg)          | 100 | 9.50          | 2.53              |
|                        |                      | 60  | 5.70          | 4.21              |
|                        |                      | 20  | 1.14          | 21.1              |
|                        |                      | 10  | 0.114         | 211               |
| 1                      | 10 (2x5mg)           | 100 | 3.17          | 7.58              |
|                        |                      | 60  | 1.90          | 12.6              |
|                        |                      | 20  | 0.38          | 63.2              |
|                        |                      | 10  | 0.04          | 632               |

### 1.7.2. Capsaicin

Topical application of capsaicin in humans initially activates cutaneous small-diameter sensory fibres, resulting in a burning sensation, erythema, and enhanced sensitivity to noxious and innocuous stimuli. However, repeated topical applications of capsaicin lead to desensitization and degeneration of epidermal nerve fibers (ENFs), which are predominantly C-fibre nociceptors. Three weeks of frequently applied low concentration (0.075%) topical capsaicin results in 80% reduction in ENF density and moderate thinning of the subepidermal neural plexus. The effect is reversible, and regeneration of

ENFs corresponds with return of the ability to detect painful sensations [Nolano, 1999]. Following capsaicin exposure, sensations mediated by non-TRPV1-expressing cutaneous nerve endings are expected to remain unaltered. [Bley, 2010] The subjects will be exposed to low levels of capsaicin for a short period of time and therefore we do not expect to see any desensitization or degeneration of ENFs.

Any irritation caused by capsaicin can be reduced by washing the area well with cold water. If necessary, the subject will be withdrawn from the treatment but will be followed until resolution of the adverse event.

### **1.7.3. Histamine**

Histamine is a pleiotropic endogenous biologically active amine that is widely distributed in the body and acts on multiple organ systems. Histamine is a mediator of immune and inflammatory reactions. Histamine is formed de novo during decarboxylation of histidine by histidine decarboxylase (histamine forming capacity or HFC) and is stored in the cytoplasmic granules of mast cells and basophils. Histamine synthesis, storage and release from endogenous pools are influenced by a variety of conditions including stress, circadian rhythms, drugs and allergens.

Endogenous histamine acts on a large variety of different cell types including smooth muscle, neurons, endocrine and exocrine cells, blood cells and cells of the immune system. Histamine covers its multiple biological actions via one of several receptors including H1, H2 and H3 and most recently, H4 receptors. The receptors have been detected in mammalian brain, respiratory tract, genito-urinary system and vascular system, as well as on several types of leukocytes and haematopoietic cells. The principal receptors throughout the body are the H1 and H2 receptors.

Histamine will be applied according to the skin prick method using 1% histamine solution.

Following application of histamine, if pruritus continues to be an issue an antihistamine or other appropriate treatment could be administered at the discretion of the PI. If necessary, the subject will be withdrawn from the treatment but will be followed until resolution of the adverse event.

### **1.7.4. Cowhage**

Proteinase activated receptors 2, PAR2 (Steinhoff, 2003), is activated exogenously by the spicules of cowhage, a tropical plant which represents a particularly valuable experimental itch inducer (Papoiu, 2011). Upon skin contact, cowhage spicules release mucunain, a cysteine protease that serves as a ligand for the PAR2 receptors [Reddy, 2008a] and elicits a strong sensation of “itch without a flare” that lasts for several minutes ( [LaMotte, 2009] and [Sikand, 2009]).

Following application of Cowhage if itch is still an issue the spicules will be removed from skin using adhesive tape.

If pruritus continues to be an issue after removal of the spicules, an appropriate treatment could be administered at the discretion of the PI. If necessary, the subject will be withdrawn from the treatment but will be followed until resolution of the adverse event.

#### **1.7.5. Other study procedures**

Other study procedures are routine and are not expected to represent a significant safety risk to participants.

## **2. OBJECTIVE(S)**

### **2.1. Part A**

#### **2.1.1. Primary Objectives for Part A**

- To assess whether any of the three doses of SB705498 are able to adequately reach the target activated by the TRPV1 agonist capsaicin

#### **2.1.2. Secondary Objectives for Part A**

- Evaluate the safety and tolerability during application of the 3 doses (1, 3 and 5%) of SB705498 compared to placebo.

### **2.2. Part B**

#### **2.2.1. Primary Objectives Part B**

- Assess the affect of SB705498 on itch intensity induced by challenge agents (cowhage and histamine) on the 0 to 100 Computerised Visual Analogue Scale (COVAS).

#### **2.2.2. Secondary Objectives for Part B**

- Assess the duration of itch intensity after stimulation with challenge agent.

## **3. ENDPOINT(S)**

### **3.1. Part A**

#### **3.1.1. Primary Endpoint Part A**

- Measurement of the area of flare induced by capsaicin as assessed by Laser Doppler Imaging (LDI)

#### **3.1.2. Secondary Endpoint Part A**

- Safety and tolerability as assessed through vital sign measurements, ECG, Clinical Laboratory data and Adverse Events.
- Intensity of flare induced by capsaicin as assessed by LDI

### **3.1.3. Primary Endpoints Part B**

- Average itch over maximum of 15 minutes post application of challenge agent (analysis of weighted means) on 0 to 100 COVAS scale.

### **3.1.4. Secondary Endpoints Part B**

- Peak itch intensity on 0 to 100 COVAS scale
- Duration of itch from time of challenge

## **4. INVESTIGATIONAL PLAN**

### **4.1. Study Design**

#### **4.1.1. Discussion of Design**

This study will be conducted as a single-centre, randomised, double-blind, placebo controlled study. This study is a double blind study where the patient, investigator and site team, i.e. clinical unit staff remain blinded to the treatment. However the GSK study team not involved with study assessments will be unblinded. The GSK study team will view unblinded data from Part A to determine whether the study should progress to Part B and what the selected dose should be. The investigator and site staff will remain blinded throughout both parts of the study. An on-site unblinded pharmacist or other authorised site staff will be utilised to dispense the study medication.

A target of a maximum of 16 subjects will be recruited into Part A of the study, 10 of the best available responders will be invited to participate in Part B. If data from 10 subjects is unable to be obtained, further subjects from Part A may be asked to participate in Part B or new subjects may be enrolled to participate in Part B only, providing they pass screening and challenge agent assessments (as described in screening assessments for Part A). Male and female subjects will be eligible for screening if they meet the inclusion/exclusion criteria described in Section [5.2](#).

At screening, participants will be required to show a response to capsaicin and to both challenge agents - cowhage/histamine. The screening visit may be split over 2 days.

Those that respond to capsaicin and both challenge agents scoring greater than 40 on the 0-100 COVAS scale will be eligible for randomization into Part A and potentially Part B of the study.

#### **4.1.2. Design of Part A**

In Part A, up to 16 healthy Caucasian volunteers will be recruited to participate in the capsaicin challenge.

Subjects will receive all three active applications of 1%, 3% and 5% of SB705498 as well as a placebo in a randomised order (1, 2, 3 and 4) on four discrete 3x3cm square patches on the volar surface of forearms as shown in [Figure 3](#). These four challenges with capsaicin will be split over 2 days.

Prior to each challenge, the topical administration of SB705498 or placebo will be left on the arm for 1 hour. Following this the capsaicin will be applied as described in Section 7 and assessments of skin blood flow (flare) will be performed using Laser Doppler Imaging (LDI). A baseline LDI scan will be performed prior to the application of the SB705498 cream and again after 1 hr once the excess cream has been wiped away. A third scan will then occur 5 minutes after capsaicin challenge (once excess capsaicin has been wiped away). A final scan will then take place 2 hours post application of the SB-705-498. This is shown in schematic format in Figure 2. We will be looking for a reduction in flare to be considered a positive study outcome. Previous research has shown oral doses of SB705498 produced a reduction in the area of capsaicin-evoked flare by ~ 35% compared with placebo, (Chizh, 2007, 132: 132-141)

#### **4.1.3. Part B**

Of the sixteen subjects randomised to participate in Part A, the ten subjects who show the most optimal treatment response during the capsaicin challenge compared to placebo will be asked to participate in Part B. If we are unable to obtain data from ten of the Part A subjects, we may ask the next best responders from Part A to go on to Part B or recruit new subjects to enter the study and participate in Part B of the study, providing they pass screening and challenge agent assessments.

Each volunteer will be randomised to receive the placebo and the selected topical application strength of SB705498 from Part A of the study for both the cowhage and histamine challenge. Each subject will participate in both a cowhage challenge and a histamine challenge with both treatment arms in a crossover fashion an example of a possible randomisation schedule is shown in Figure 2. Each subject will receive two doses of SB705498 over 2 days.

The cowhage challenge will be performed on a separate day to the histamine challenge.

**Figure 2 Schematic of Part B – Cowhage/histamine challenge**

[figure not shown]

#### 4.1.4. Cowhage/ Histamine Challenge

Subjects will be randomised to receive either the SB705498 cream or placebo treatment first. This will be applied to the volar surface of the forearm followed 1 hour later by the cowhage/ histamine stimulant. Subsequently once all itch sensations have subsided the other treatment (placebo or SB705498) will be applied to the corresponding area on the other forearm and the same stimulant (cowhage/ histamine) will be applied as before.

This whole procedure will be repeated for the remaining challenge agent, cowhage/histamine on the following day allowing time for previous itch sensations to completely subside. For each challenge agent itch intensity will be rated using the COVAS scale as previously described commencing 1-2 mins before the challenge agent is applied.

## 4.2. Treatment Assignment

Subjects will be assigned to a treatment sequence in accordance with the randomisation schedule generated by Clinical Statistics, prior to the start of the study, using validated internal software.

### Part A

Subjects in Part A of the study will follow a Williams Design of a generalised latin square and will be randomised to one of the following sequences: 1 2 4 3, 2 3 1 4, 3 4 2 1 or 4 1 3 2 in a 1:1:1:1 ratio where one of the numbers will be placebo and the other 3 will represent each of the three active doses of SB705498.

The first number in the sequence will be applied to the first application site as shown in [Figure 3](#). Each subsequent number will be applied to the next application site.

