2. LDI scan will be performed after application of SB705498 cream or placebo. Cream is applied, left for 1 hr and excess is then removed to allow scanning.
3. LDI scan will be performed 5 mins after the Capsaicin cream is wiped off the arm.
4. Application of the cream/placebo followed by capsaicin challenge and LDI scanning will be performed twice on each day. i.e. 4 applications over the 2 days with the 3 different doses of SB705498 and placebo.

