#### 4.5.2. Capsaicin challenge detailed schedule- Part A

The table below is based on an example randomization schedule for reference only. Each subject will be assigned an individual randomization schedule detailing which dose will be given in which order

| Procedure                           | Study Day (per treatment arm) |                |                |         |                |                |                |         |                |                |                |         |                |                |                |         |
|-------------------------------------|-------------------------------|----------------|----------------|---------|----------------|----------------|----------------|---------|----------------|----------------|----------------|---------|----------------|----------------|----------------|---------|
|                                     | Day 1 AM                      |                |                |         | Day 1 PM       |                |                |         | Day 2 AM       |                |                |         | Day 2 PM       |                |                |         |
|                                     | 0                             | 60 min         | 95 min         | 120 min | 0              | 60 min         | 95 min         | 120 min | 0              | 60 min         | 95 min         | 120 min | 0              | 60 min         | 95 min         | 120 min |
| Administration of SB705498 cream 1% | X                             |                |                |         |                |                |                |         |                |                |                |         |                |                |                |         |
| Administration of SB705498 cream 3% |                               |                |                |         | X              |                |                |         |                |                |                |         |                |                |                |         |
| Administration of SB705498 cream 5% |                               |                |                |         |                |                |                |         | X              |                |                |         |                |                |                |         |

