## **5. STUDY POPULATION**

### **5.1. Number of Subjects**

Sixteen subjects will be randomised to take part in Part A of the study. From these sixteen subjects, ten subjects who show the most optimal treatment effect compared to placebo on the selected dose will be asked to participate in Part B. If for any reason these subjects are unable to participate in Part B, other subjects from Part A with sufficient treatment effect will be asked to participate to ensure 10 subjects in Part B. Additional subjects may be enrolled into Part B to ensure 10 completers in Part B. If subjects prematurely discontinue the study, additional subjects may be enrolled as replacement subjects and assigned to the same treatment sequence at the discretion of the sponsor in consultation with the investigator.

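### Part A's single Williams square, run as two same-day pairs, never tests one of the three doses on the same day as placebo

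*Protocol*

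**What the plan says.** Protocol section 4.2 states that Part A "will follow a Williams Design of a generalised latin square", and lists four orders: "1 2 4 3, 2 3 1 4, 3 4 2 1 or 4 1 3 2 in a 1:1:1:1 ratio". One code stands for the placebo cream and the remaining codes for the 1%, 3% and 5% strengths. Section 5.1 sets the size: "Sixteen subjects will be randomised to take part in Part A of the study". That gives four subjects per sequence.

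On timing, section 4.1.2 says "These four challenges with capsaicin will be split over 2 days", and footnote 4 to the Time and Events Table (section 4.5.1) says the cycle "will be performed twice on each day. i.e. 4 applications over the 2 days". Section 4.5.2 sets the four periods out as Day 1 AM, Day 1 PM, Day 2 AM and Day 2 PM. Its order of doses is an illustration only ("The table below is based on an example randomization schedule for reference only"). Neither the AM-to-PM gap nor a washout is stated.

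Sections 1.5.1 and 4.1.2 choose the Part B dose by the size and consistency of its flare reduction against placebo. Section 6.2.4 plans a dose-response model first. If the data do not allow one, it plans a mixed model with treatment, period, time and treatment by time as fixed effects and subject as the random effect.

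**The concern.** Part A compares each dose with placebo in order to pick one. A four-period Williams square treats the periods as equally spaced. Here periods 1-2 and 3-4 fall within a day, and only the step from 2 to 3 crosses a night. If a subject's capsaicin response varies from day to day, a comparison made within a day is cleaner than one made across days, so the three doses should have equal access to same-day placebo. Otherwise one dose may look less consistent because of the code number it was given. Section 5.1 then ranks subjects for Part B on their effect against placebo at the selected dose, so the extra noise would carry forward.

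**Working it through.** **Inputs.** Four sequences at 1:1:1:1 (4.2); 16 subjects (5.1); two applications per day (4.1.2, 4.5.1, 4.5.2); within-subject CV 0.45 and stated precision 37.7% (6.2.1). Assumptions: one code-to-treatment mapping for all subjects, which is the plain reading of 4.2, and a subject-by-day variance of ρ times the residual variance with ρ = 0.25, 0.5 or 1, because the protocol gives no figure.

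**1. The plan's own figure.** Half-width = exp(t × s × √(2/16)) − 1 with s = √ln(1 + 0.45²) = 0.429. The protocol gives no degrees of freedom; 17 to 18 give 37.8% to 37.6%, so 37.7% is reproduced. The factor 2/16 is the same for all three doses.

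**2. Same-day pairs.**

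| Sequence | Day 1 | Day 2 |
|---|---|---|
| 1 2 4 3 | 1, 2 | 4, 3 |
| 2 3 1 4 | 2, 3 | 1, 4 |
| 3 4 2 1 | 3, 4 | 2, 1 |
| 4 1 3 2 | 4, 1 | 3, 2 |

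Pairs 1-2, 2-3, 3-4 and 1-4 share a day in 8 of 16 subjects each; pairs 1-3 and 2-4 in 0 of 16. Whichever code is placebo, two doses share its day in half the subjects and one never does. Each treatment still falls on each day, and in AM and in PM, in 8 of 16 subjects, and each of the 12 ordered neighbour pairs occurs once. However, the neighbour pairs 1-3 and 2-4 occur only overnight and the other eight ordered pairs only within a day.

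**3. Variance, subject-only model.** A within-subject difference has variance 2 within a day and 2 + 2ρ across days, in units of the residual variance. If a fraction f of subjects have dose and placebo on different days, the contrast variance is (2 + 2ρf)/16. Here f = 1 for the never-same-day dose and 0.5 for the others.

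| ρ | Never same day, (2+2ρ)/16 | Other two, (2+ρ)/16 | Ratio | Interval width ratio |
|---|---|---|---|---|
| 0 | 0.1250 | 0.1250 | 1.00 | 1.00 |
| 0.25 | 0.1563 | 0.1406 | 1.11 | 1.05 |
| 0.5 | 0.1875 | 0.1563 | 1.20 | 1.10 |
| 1 | 0.2500 | 0.1875 | 1.33 | 1.15 |

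**4. With a subject-by-day random effect** (generalised least squares, period fixed), the variances are 0.1500 v 0.1375, 0.1667 v 0.1458 and 0.1875 v 0.1562: ratios 1.09, 1.14 and 1.20.

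**5. Coverage of the subject-only 95% interval.** That model gives all three contrasts the average variance, (2 + 4ρ/3)/16 = 0.1458, 0.1667 or 0.2083. For the never-same-day dose this is 0.933, 0.889 or 0.833 of the true variance. With one value per application there are 64 − 16 − 3 − 3 = 42 degrees of freedom and t = 2.018, so the effective multiplier is 2.018 × √0.933 = 1.95, then 1.90 and 1.84. Coverage is about 94.2%, 93.6% and 92.7%, and simulation agrees. The other two doses cover 95% to 96%.

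**6. Carry-over within a day only.** Let L be the effect left by each code, with placebo coded 1. The bias is (L1 + L3 − L2 − L4)/4 for codes 2 and 4, and 0 for code 3. If each active leaves c and placebo none, it is −c/4, 0 and −c/4; with equal gaps it would be −c/4 for all three. If all four codes leave the same effect, it is zero.

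**The case against.** The pairing count is exact, so the argument is about consequence. Several points on the other side stand.

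- A day effect common to all subjects is absorbed by the period term. Only variation that differs between subjects by day, or carry-over that depends on both treatment and gap, does harm. The protocol sizes neither.
- Each application has its own baseline scan, and flare is defined against that baseline (7.3, 7.3.1), so day-level shifts in resting blood flow are at least partly removed.
- Creams go on separate patches, and less than 10% of the drug is expected in plasma (1.7.1). A common effect of the capsaicin challenge cancels in step 6.
- Part A tests no hypothesis (6.1.1), and its stated precision is already ±37.7%.
- The subject-only model is the fallback, and section 6.2.4 allows an appropriate variance structure. A reader might infer that the planned interval is definitely too narrow for one dose; the text does not go that far.

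A reader might also infer that one dose's estimate is biased, or that the design is not a Williams square. Neither follows: subject-by-day variation changes precision, not expectation, and the square has its usual properties.

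What remains is an avoidable inequality in the comparison that selects the dose.

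**Conclusion.** The concern holds as a moderate weakness of the design. One dose never shares a day with placebo in any subject, while the other two do in half; this follows from the listed sequences and the two-per-day schedule alone. The cost depends on an unknown. For ρ between 0.25 and 1, that dose has 11% to 33% more variance under the subject-only fallback (9% to 20% with a subject-by-day term), and its subject-only interval covers about 94% to 92.7%. At ρ = 0 with no gap-dependent carry-over, the cost is nil.

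It would be tempting to conclude that the code number decides which dose goes forward. The documents do not support that: it can influence how consistent a dose appears, by an amount they do not let us fix. The conclusion assumes one code mapping for all subjects.

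**What to change.** Randomise Part A in blocks of four subjects, each block one complete Williams square, rotating through:

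- 1243, 2314, 3421, 4132 (as listed; 1-3 and 2-4 never share a day)
- 1342, 3214, 2431, 4123 (1-2 and 3-4 never share a day)
- 1234, 2413, 4321, 3142 (1-4 and 2-3 never share a day)

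Repeat one square for the fourth block, and include a subject-by-day random effect in the fallback mixed model of section 6.2.4.

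Over 12 subjects every pair shares a day in 4, and the three dose-placebo variances are equal. At 16, the fraction on different days is (8 × 1 + 8 × 0.5)/16 = 0.75 for the dose that misses placebo in the repeated square, and (4 × 1 + 12 × 0.5)/16 = 0.625 for the other two. The variance ratio is (2 + 1.5ρ)/(2 + 1.25ρ), an excess of 2.7%, 4.8% or 7.7%. The average variance of the three contrasts under the subject-only model is unchanged at (2 + 4ρ/3)/16.

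The cost is a longer randomisation list; no subjects, visits or procedures are added. Period balance is kept if Part A stops after any complete block, although equal day-pairing is reached only at 12.

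The change does not guarantee less carry-over bias. If each active leaves the same same-day effect c, the 12-sequence set shifts all three doses equally, by −c/6. If the effect scales with strength (1:3:5, with 5% leaving 1 unit), the shifts are −0.033, −0.10 and −0.167, a spread of 0.133. The listed square gives a spread of 0.05, 0.15 or 0.35 depending on coding. The case for the change therefore rests on equal precision.
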